**Safty and monitoring board**

An independent Ethics Committee of Zhongshan Hospital (ECZH) ,Fudan University approved the protocol for the trial and is responsible for monitoring the accumulated interim data as the trial progresses to ensure patient safety and to review efficacy. In addition, the committee is charged with reviewing the quality and timeliness of data collection. Interim data on safety measures requested by the ECZH are reviewed at each of the scheduled semi-annual meetings. Serious adverse events are reviewed by the ECZH as they occur and the ECZH reviews quarterly reports about the count of patients who present hepatic or renal toxicities during the study. One interim efficacy analysis of the primary outcome measure is planned to occur when approximately 50% of the data are complete or when approximately 90 of the 180 patients have completed baseline and 16 week MRS examination. O'Brien-Fleming statistical stopping guidelines for efficacy apply

**4.3 Outcomes**

The primary outcomes are the changes in OGTT (glucose, insulin, AUC of glucose), HbA1c; lipid profile（TC, TG, HDL-c, LDL-c, ApoA, ApoB, ApoE, Lpa); liver enzymes (ALT, AST, γ-GT, ALP). The secondary outcome is liver fat content by 1H NMR spectroscopy.

Safety endpoint includes serious adverse events and non-serous adverse events. Adverse event collection was conducted at each visit after baseline. No specific laboratory safety tests are required during this study. However, if a laboratory abnormality is clinically relevant or leads to an adverse event report, specific appropriate actions may be required. ECG will be performed at the beginning and end of the study.

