| **Randomization:** | The statistical group of Public Health College, Fudan University took responsibility for the preparation and administration of randomization plan. Randomization sequence was generated by SAS8 computer software in a three-center, group randomization manner, and the whole procedure was finished by statistical staff who were not engaged in the study. An envelop randomly labeled with drug assignment was issued only if the database showed that the patient was eligible, had signed the consent statement, and had all required baseline data keyed to the database. The randomization scheme assigned patients to join in one group and accept specific treatment. |
| **Primary Endpoint:** | changes in OGTT (glucose, insulin, AUC of glucose), HbA1c; lipid profile（TC, TG, HDL-c, LDL-c, ApoA, ApoB, ApoE, Lpa); liver enzymes (ALT, AST, γ-GT, ALP). |
| **Study Duration for Each**  **Subject:** | Each subject is followed for 16 weeks; the trial will be completed in 3 year |
| **Number of Centers:** | Three clinical centers in China |
| **Sample Size:** | 180 subjects |
| **Primary Statistical Analysis:** | Statistical analyses will follow the intention-to-treat paradigm, which means that all randomized patients with baseline and 16 week liver enzyme, OGTT, HbA1c,lipid profile and MRS hepatic fat content will be included in the treatment group to which they were assigned. Any randomized patient who does not have the requisite data will be considered unimproved on the primary outcome measure and compared by assigned treatment group. Given the fact that there were two planned primary comparisons, bonferroni-adjusted P values of less than 0.025 were considered to indicate statistical significance. Comparisons of the continuous measures before and after treatment were made with a paired t-test, and the differences from baseline to 16 weeks in BBR plus lifestyle intervention group or PGZ plus lifestyle intervention group were compared with the pure lifestyle intervention group using the analysis of co-variance model respectively, in order to adjust for baseline value. |

1. **STUDY FLOWCHARTS**
   1. **Trial Design**

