**10.2 Sample Size Estimation**

The planned sample size for the trial was 180 patients with equal allocation to each of the three treatment groups (60 per group). The sample size estimates were based upon a two-group, binomial comparison of the proportions of patients satisfying the decrease in liver fat content over the course of treatment either with pioglitazone or berberine. Since our current study had three treatment groups and two primary hypotheses, the assumption was made that the two primary comparisons, pioglitazone vs. no-drug control and berberine vs. no-drug control, required the type I error estimate be reduced from 0.05 to 0.016 in accordance with three-group comparison. Expected proportions improved were speculated using pilot data from pioglitazone-treat NAFLD studies. There were no available data at the time of study design to estimate liver steatosis response with berberine, which was assumed, for purposes of planning the trial, to be the same as for pioglitazone.

The sample size calculations were performed using the formula: n1=n2=2[(tα+ t2β)s/δ]^2^ with a standard deviation of NAFLD patients liver fat content (s=6.87%, from our prior study), with an expected difference in proportion of improvement between pioglitazone or berberine group and the control group (δ=0.05), with an α level of two-sided type I error (0.016, corrected for three-group comparison), and with a β level of type II error (0.10; i.e., 90% power). The number per group, using the above assumptions was 52. Inflating this number by the 15% expected missing data rate yielded approximately 60 patients per group, or a total of 180 for the trial.

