**10.3 Statistical Analyses**

Statistical analyses for the two primary hypotheses will follow the intention-to-treat paradigm, which means that all randomized patients with baseline and 16 week liver enzyme, OGTT, HbA1c,lipid profile and 1H MRS hepatic fat content will be included in the treatment group to which they were assigned. Missing values will remain missing and patients will be censored at their last follow‐up assessment.

The chi-square test and analysis of covariance or Kruskal-Wallis H test were used to compare baseline variables among the groups for categorical and continuous variables, respectively. Comparisons of the continuous measures before and after treatment were made with the use of a paired t-test, and the differences from baseline to 16 weeks in BBR plus lifestyle intervention group or pioglitazone plus lifestyle intervention group were compared with the lifestyle intervention group using the analysis of co-variance model respectively, in order to adjust for baseline value. Given the fact that there were two planned primary comparisons, bonferroni-adjusted P values of less than 0.025 were considered to indicate statistical significance.

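### The 0.025 threshold corrects for the two drug comparisons but not for the 16 primary measures tested in each

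*Protocol*

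**What the plan says.** Section 4.3 opens with "The primary outcomes are the changes in OGTT (glucose, insulin, AUC of glucose), HbA1c; lipid profile". It spells out the lipid profile as "TC, TG, HDL-c, LDL-c, ApoA, ApoB, ApoE, Lpa" and continues with "liver enzymes (ALT, AST, γ-GT, ALP). The secondary outcome is liver fat content by 1H NMR spectroscopy". The synopsis gives the same list as its primary endpoint ("changes in OGTT (glucose, insulin, AUC of glucose), HbA1c; lipid profile", followed by the lipids and enzymes), and sections 3.1 and 4.1 repeat it.

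For the analysis, section 10.3 says that changes to week 16 in each drug group "were compared with the lifestyle intervention group using the analysis of co-variance model respectively, in order to adjust for baseline value". It then sets the threshold: "Given the fact that there were two planned primary comparisons, bonferroni-adjusted P values of less than 0.025 were considered to indicate statistical significance". The synopsis states the same rule. Section 10.2 shows which comparisons are meant: "the two primary comparisons, pioglitazone vs. no-drug control and berberine vs. no-drug control, required the type I error estimate be reduced from 0.05 to 0.016".

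No section ranks the 16 measures, gives an order of testing, says whether one or all must be significant, or divides alpha among them. The synopsis (on missing data) and the monitoring-board text (on the interim analysis) refer to a primary outcome measure in the singular, which does not fit the list.

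**The concern.** A Bonferroni divisor has to match the number of chances to claim success. Here the divisor is two, the number of drug-versus-control contrasts, but each contrast is tested on 16 measures that the protocol calls primary. As written, the rule gives the appearance of a 5% error rate without delivering it. With both drugs inactive, a report could still truthfully say that a primary outcome met the pre-specified threshold, and the protocol would give no ground for discounting it.

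This is more than a detail left for the SAP. The protocol itself fixes the list, the threshold and the reason for the threshold, and these do not fit together. An SAP that followed section 10.3 faithfully would carry the gap forward.

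**Working it through.** **Inputs from the protocol**

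- Measures (section 4.3): OGTT glucose, insulin and AUC of glucose (3), HbA1c (1), lipids (8), liver enzymes (4). 3 + 1 + 8 + 4 = 16.
- Drug-versus-control comparisons (section 10.2): 2.
- Primary tests: 16 × 2 = 32.
- Threshold per test (section 10.3): 0.025.
- Three equal arms with one shared control (sections 6 and 10.2).

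**The plan's own figure.** 0.05 / 2 = 0.025. For two independent tests the family-wise error is 1 − 0.975² = 4.9%. The threshold is therefore right for one measure and two drugs.

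**Applied to the listed endpoint, treating tests as independent**

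- One drug, 16 measures: 1 − 0.975^16 = 33.3%.
- Two drugs, 32 tests: 1 − 0.975^32 = 55.5%.
- Expected false positives with no effect: 32 × 0.025 = 0.8. This does not depend on correlation.

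**Allowing for correlation.** The protocol gives no correlations between measures, so the values below are assumptions. Each row is a simulation of 400,000 trials with normal test statistics, three equal arms, a shared control and no drug effect. It counts trials with at least one of the 32 two-sided tests below 0.025.

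| Assumed correlation between measures | P(at least one false positive) |
|---|---|
| 0 | 53% |
| 0.3 | 46% |
| 0.5 | 37% |
| 0.7 | 26% |
| 0.9 | 14.5% |
| Strong for overlapping measures (such as TC/LDL-c/ApoB, ALT/AST, glucose/AUC), 0.05 to 0.2 for unlisted pairs | 44% to 46% |

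**The alpha in section 10.2 does not close the gap.** The sample size uses 0.016, also derived from the number of groups. Applied to 32 independent tests it gives 1 − 0.984^32 = 40%.

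**Sixteen is a minimum.** OGTT glucose and insulin could each be tested at several time points. With 18 measures (36 tests) the independent figure is 1 − 0.975^36 = 59.8%.

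**Threshold that would cover all 32 tests.** 0.05 / 32 = 0.0016, with a family-wise error of 1 − (1 − 0.0015625)^32 = 4.9% under independence.

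**The case against.** The strongest reply is that the error rate depends on a success rule that the protocol does not state. The figures count a win on any one of 32 tests. If all 16 measures had to be significant for a drug, type I error would not be inflated. The SAP, which section 10.1 says holds the complete details, might contain such a rule or a testing order. This stands as a limit: the figures are conditional on the any-win reading. It does not rescue section 10.3, whose stated reason for 0.025 counts the drugs and not the measures.

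A reader might go further in three ways that the documents do not support.

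- **That a false positive is close to a coin toss.** This is only the low-correlation end. Several measures overlap heavily, and with uniformly strong correlation the figure falls to about a quarter or less.
- **That under an all-must-succeed rule the trial would have some specific, low power.** The protocol gives no effect size or standard deviation for any of the 16 measures. Its 90% power refers to liver fat, a secondary outcome, so no such figure can be derived.
- **That the before-and-after paired t-tests in section 10.3 add to the count of primary tests.** They are described there as within-group comparisons and are not made primary hypotheses. They are not part of the 32.

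**Conclusion.** The concern holds. The protocol declares at least 32 primary tests and corrects for two. If any significant measure counts as a primary finding, the family-wise error with no drug effect is about 26% to 53% for assumed correlations of 0.7 to 0, and about 14.5% even at 0.9, against an intended 5%. The exact value rests on assumed correlations, but the direction does not: every value examined is close to three times the intended rate or more. The mismatch bears on the trial's main confirmatory claim and cannot be credibly repaired once results are known, so it should be resolved before the interim efficacy analysis.

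**What to change.** **Preferred.** Name one primary measure, consistently in the synopsis and sections 3.1, 4.1, 4.3 and 10.3. Test it for the two drug-versus-control comparisons at 0.025 each and make the other measures secondary. The existing Bonferroni rule is then correct, since 2 × 0.025 = 0.05. MRS liver fat is a candidate, because section 10.2 sizes the trial on it and the interim analysis is timed by completed MRS examinations. Choosing it would change the primary objective stated in section 3.1, so this is a substantive decision and not only an edit.

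**Alternative.** Keep all 16 measures primary and replace the plain 0.025 rule with Holm across the 32 tests, starting at 0.05 / 32 = 0.0016.

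Either way, the same revision should reconcile the 0.025 in section 10.3 with the 0.016 in section 10.2, and say which measure the O'Brien-Fleming interim rule applies to and how that look fits within the chosen level.

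**Cost.** No new data are needed. The first option leaves fewer confirmatory claims on individual lipids, enzymes and glucose measures. The second costs power. As an illustration only, take the liver-fat planning effect (difference 5, SD 6.87, 52 per group). The expected test statistic is (5 / 6.87) × √(52 / 2) = 3.71, and the critical value at 0.0016 is 3.16. Power at the first Holm step is then Φ(3.71 − 3.16), about 71%, and 90% would need about 75 evaluable patients per group. The corresponding loss for the 16 listed measures cannot be calculated from the protocol.

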**4.4 Specimen banking**

Specimens are collected and stored in a central repository for use as approved by the Committee of the trial, endocrine department of Zhongshan Hospital. Specimens include serum, urine and DNA. The blood samples collected at screening visit, and at 4, 8, 12 and 16 week visits are divided into 0.5mL aliquots and stored frozen at −70 °C. Additional blood was collected at the screening visit for extraction of DNA which is stored at −20 °C.

**5. Participant Selection**

During the course of the trial, 180 eligible adults will be identified and recruited from unsolicited referrals to the three participating clinical centers.

**5. 1 Inclusion Criteria**

1.Patients must have an age range between 18 to 65 years(inclusive).

2. Patients with Liver fat content assessed by 1H MRS≥13%.

3. Patients must meet the criteria for impaired glucose regulation or type 2 diabetes mellitus(FPG≥5.6mmol/L and/or a two hour glucose value≥7.8mmol/L) .Patients with a HbA1c＞7.5% will be excluded from the study.

4.Course of diabetic mellitus less than 1 year

5. Informed consent signed

**5. 2 Exclusion Criteria**

1.Any causes of chronic liver disease other than NAFLD(such as-but not restricted to- alcohol or drug abuse, medication, chronic hepatitis B or C, autoimmune, etc.);

2. Patients with significantly impaired liver function: ALT or AST≥2 times upper limit of normal;

3. HBsAg(+) and/or HCV-Ab(+), or other liver diseases;

4. Patients with type 1 diabetes mellitus or gestational diabetes or special type diabetes, and patients with BMI＜22Kg/m2;

5. Course of diabetes more than 1 years;

6. Diabetics patients who have taken or are taking oral glucose-lowering drugs or insulin;

7. Diabetics patients with a HbA1c＞7.5% on initial visit;

8. Patients with severe diabetes complications(diabetes ketoacidosis, diabetes coma or with symptomatic of diabetes coma; dysfunction of nerve, retinopathy, dysfunction of kidney);

9. Patients with serum creatinine ≥1.5mg/dL(133umol/L);

10. Patients with a history of cilinically significant heart disease(myocardial infarct, heart failure, and/or severe cardiac rhythm);

11. Complicating severe infection,within 6 months after operation, severe trauma;

12. Patients with excess alcohol consumption≥140g/week(male); ≥70g/week(female);

13. Patients have participated other clinical trials within 24 weeks;

14. Patients with a history of drug allergy to TZDs and berberine;

15. Patients with gestation or possible gestation or lactation, or males or females expecting gestation during clinical trial;

16. Mental diseases patients;

17. Those who refuse to sign informed consent;

18. Any other conditions, which, in the opinion of the investigators would impede compentence or compliance or possiblity of hindering completion of the study;

19. Patients with serum triglyceride≥5.0mmol/L;

20. Patients with thyroid disease, including hyperthyroidism or hypothyroidism.

**6. Treatments**

Patients who signed an informed consent statement and who met the eligibility criteria were randomly assigned to one of three groups for 16 weeks of treatment:

Group 1: Pioglitazone (15 mg q.d.) and Life style intervention

Group 2: Berberine (0.5g, t.i.d.) and life style intervention

Group 3: Life style intervention only without drugs

Pioglitazone (Actlns®, Taiyang Pharmaceuticals Beijing, China, Inc.) is administered as a single tablet of 15 mg per day orally 30 minutes before the morning meal. The rationale for choosing this dosage was based upon earlier pilot studies that examined the safety and efficacy of pioglitazone in patients with NAFLD[22-25].

Berberine ( Berberine®, Huashi Pharmaceuticals Shanghai, China, Inc.) is administered three times a day, at a dosage of 0.5g orally each time. The berberine dose chosen for this trial (0.5g t.i.d) is more than the dose recommended clinically, but still within the range of safety that has been tested in previous studies[27,28].

In addition to study medications, participants receive standardized recommendations concerning life-style modification (dietary modification, weight loss, exercise), use of prescription or non-prescription medicines or herbal remedies or dietary supplements, consumption of alcohol, and management of various co-morbid illnesses. All participants follow calorie limited diet that subtracts 500kcal from daily mean calorie intake before entering the treatment (daily mean calorie intake is calculated through diet diary during screening period) and are required to keep daily food diaries. We also provide participants with general recommendations to achieve more than 150 min medium intensity aerobic exercise per week with heart rate around 50-70% maximum, or more than 90 minutes higher-intensity aerobic exercise per week with heart rate around 70% maximum.

**7. Study Drug Handling**

**7.1 Supply and Storage**

The drugs used in the trial, pioglitazone and berberine, were purchased from the pharmceutical companies to ensure the same lot number. All investigational drug supplies in the study will be stored in a secure, safe place, under the responsibility of the Investigator or other authorized individual, and under the conditions described on the labeling.

**7.2 Dispense and management**

The investigator should dispense the specific drugs determined at randomization to eligible participants at each visit from V0 to V4 and count the tablets returned by the participant. It is the investigator’s responsiblility to ensure that an accurate record of invesigational product issued and retured is maintained.

**7.3 Prohibited Concomitant Treatment**

Participants are not allowed any prescription or over-the-counter medication or herbal remedy to improve NAFLD or IGR/T2DM during screening and treatment phase of the trial. The anti-NAFLD agents are defined as lipid-regulating drugs(statins, fibrates), silybin, ursodeoxycholic acid, Polyene Phosphatidylcholine, Vitamin E, and some herbs regulating lipid and protecting liver function. The anti-IGR or T2DM includes insulin, insulin sensitizer (Rosiglitazone), sulfonylureas, biguanides, α-glycosidase inhibitors.

**7.4 Treatment Accountability and Compliance**

Compliance will be assessed by counting returned tablets at each visit. The investigator (or delegates) will complete the appropriate page of the CRF or study drug inventory log form. The date of study drug interruption must also be recorded.

**7.5 Treatment Discontinuation**

The investigational product (IP) should be continued whenever possible. If the IP is stopped, it should be determined if the discontinuation can be made temporarily; permanent IP discontinuation should be a last resort. Any IP discontinuation should be fully documented in the CRF. In any case, the patient should remain in the study as long as possible.

Pregnancy will lead to definitive treatment discontinuation in all cases.

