**1.2 Schedule of Activities and Assessments**

| Assessment/procedure | **screening（V0）** | **Weeks from randomization** | | | | |
| --- | --- | --- | --- | --- | --- | --- |
|  |  | **V1** | **V2** | **V3** | **V4** | **V5** |
|  | **-4 week** | **0 week** | **4 week** | **8 week** | **12week** | **16week** |
| Consent | ● |  |  |  |  |  |
| Screening questionnaire | ● |  |  |  |  |  |
| Baseline medical history | ● |  |  |  |  |  |
| Follow up medical history | ● | ● | ● | ● | ● | ● |
| Inclusion/exclusion criteria | ● | ● |  |  |  |  |
| Randomization |  | ● |  |  |  |  |
| Health education & diet guide |  | ● | ● | ● | ● | ● |
| Review of concomitant drugs |  |  | ● | ● | ● | ● |
| Review for adverse effects |  |  | ● | ● | ● | ● |
| Drug dispensing |  | ● | ● | ● | ● |  |
| Review of drug adherence |  |  | ● | ● | ● | ● |
| Nutrition questionnaire |  | ● |  |  |  | ● |
| Activity questionnaire |  | ● |  |  |  | ● |
| Physical exam (Detailed/Focused) | D | F | F | F | F | D |
| OGTT with insulin |  | ● |  |  |  | ● |
| Fasting glucose/2h after meal | ● |  | ● | ● | ● |  |
| Fasting lipid profile | ● | ● |  |  |  | ● |
| Liver and renal fuction | ● | ● | ● | ● | ● | ● |
| Blood and urine routine |  | ● | ● | ● | ● | ● |
| HbA1c | ● |  |  |  |  | ● |
| Pregnancy test (females) |  | ● |  |  |  | ● |
| Serum, plasma for banking | ● | ● | ● | ● | ● | ● |
| Hepatic virus anti-body（HBsAb、HCV-Ab） | ● |  |  |  |  |  |
| ECG | ● |  |  |  |  | ● |
| Liver fat content（MRS） | ● | ● |  |  |  | ● |

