**9.2 Visit 1 (V1)**

Evaluation before randomization will include patient demographic information, medications, diet and exercise information, past medical history, family history, cigarette and alcohol use, and physical examination. Laboratory tests will be performed (liver and renal function, OGTT blood glucose + insulin, HbA1c, lipid profile, blood and urine routine, urine pregnancy test and hepatic fat content by 1H MRS).

The statistician will develop a master randomization list, with stratification blocked to assure an equal distribution of treatments at each participating site. A study number will correspond to a specific medication packet. This identifying number will be coded on the enrollment confirmation.

The patient will receive 4-week study medication and be instructed how to take the study medication. Time of first study drug administration will be recorded. Study drug will be started the next day after randomization. participants receive standardized recommendations concerning life-style modification (dietary modification, weight loss, exercise).

 An appointment will be made for next study visit (4 weeks after randomization).

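### Pregnancy is an absolute reason to stop study drug, but no pregnancy test is scheduled at weeks 4, 8 or 12, when drug is re-dispensed; a minor, inexpensive safety gap

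*Protocol*

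**What the plan says.** Protocol section 7.5 makes continuation the default: "The investigational product (IP) should be continued whenever possible". Permanent stopping is a last resort, with one condition singled out: "Pregnancy will lead to definitive treatment discontinuation in all cases". Section 7.5.2 lists the pregnancy-related stopping reasons: a positive serum test, a wish to become pregnant, and ceasing contraception.

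In section 1.2 the row "Pregnancy test (females") is marked at V1 (week 0) and V5 (week 16) only. The dispensing row is marked at V1, V2, V3 and V4 (weeks 0, 4, 8 and 12). The visit text agrees. Section 9.2 lists "urine pregnancy test and hepatic fat content by 1H MRS" among the V1 tests, and section 9.6 lists a urine pregnancy test at V5. Sections 9.3, 9.4 and 9.5 list none, yet each has the investigator dispense drug.

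On timing, section 9.2 says: "Study drug will be started the next day after randomization". The third arm takes no drug (section 6: "Group 3: Life style intervention only without drugs").

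**The concern.** The protocol itself treats pregnancy on study drug as unacceptable, and it lists a positive test among the reasons to stop. The two scheduled tests, however, lie at the ends of treatment. The first precedes any exposure. The second follows the last supply, so a positive result there would record an exposure rather than prevent one. In between, the stop depends on what the patient reports or on a test that nobody is prompted to order.

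What is at stake is participant safety in the two drug arms. A woman who conceives after V1 without knowing it could receive a further supply. The documents give no figure for embryo-fetal risk with either drug, and none is assumed here. Sample size, power, type I error and the efficacy comparisons are not involved.

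**Working it through.** The protocol states no figure on this point to reproduce. The check is a side-by-side reading of section 1.2 and sections 9.2 to 9.6, followed by simple counts.

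**Tests against dispensing**

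| Visit | Week | Pregnancy test scheduled | Drug dispensed |
|---|---|---|---|
| V1 | 0 | yes | yes |
| V2 | 4 | no | yes |
| V3 | 8 | no | yes |
| V4 | 12 | no | yes |
| V5 | 16 | yes | no |

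- Dispensings with a test at the same visit: 1 of 4 (V1). Without: 4 − 1 = 3.
- Interval between scheduled tests: 16 − 0 = 16 weeks, the whole treatment period.
- Drug re-issued without a scheduled test: 3 × 4 = 12 weeks, assuming that the four-week supply stated for V1 is repeated at V2 to V4.

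**Could the table have been misread?** The table and the visit text agree at all five visits. The row "Blood and urine routine" is marked at V2 to V4, but it does not stand for a pregnancy test, because sections 9.2 and 9.6 list the pregnancy test separately from urine routine. Section 7.2 has dispensing begin at V0, which disagrees with the table, but this does not affect V2 to V4.

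**Who is concerned.** Section 10.2 plans "equal allocation to each of the three treatment groups (60 per group"). Two arms receive drug, so 2 × 60 = 120 patients. The protocol gives no sex or age split beyond the 18 to 65 entry range, so the share of females who could become pregnant is an assumption, shown as a range.

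**Cost of a test at V2, V3 and V4**

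- Strips = 3 × number of such women.
- Ceiling, if every drug-arm patient were such a woman: 3 × 120 = 360.

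| Assumed share of the 120 | Women | Strips |
|---|---|---|
| 10% | 12 | 36 |
| 25% | 30 | 90 |
| 50% | 60 | 180 |

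These shares size the cost of the change. They do not estimate pregnancies or harm. With the added tests, the longest interval between scheduled tests falls from 16 weeks to 4.

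**The case against.** The strongest reply is that nothing here is contradictory. Section 7.5 says what to do once pregnancy is known. It does not promise detection every four weeks, and no section makes dispensing conditional on a negative test. The table and text agree on the chosen frequency. That is correct, and it is why the point is one of design rather than an error.

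The safeguards are also real. Exclusion 15 bars pregnancy, possible pregnancy and planned pregnancy. V1 has a test before the first dose. Follow-up history and adverse-effect review take place at the very visits where drug is re-dispensed. Section 7.5.2 stops drug when contraception ceases or pregnancy is wished for, which is before conception. An unscheduled test is always possible. Consent pages are not available for this review and may hold contraception or reporting instructions. All this narrows the gap. What remains is the unrecognised, unintended pregnancy, because the exclusion applies at entry and the later safeguards depend on the patient's own knowledge and report.

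Two stronger readings are tempting. A reader might infer that a woman who conceives after V1 will be given more drug at her next visit. The documents do not support that: it assumes that history-taking fails, and the stop applies however the pregnancy is found. A reader might also infer that naming a serum test in section 7.5.2, while sections 9.2 and 9.6 schedule urine tests, leaves a pregnant woman on drug. It does not, since section 7.5 covers every pregnancy. The serum test can reasonably be read as confirmation of a urine screen. Making it optional could let a false-positive strip end treatment permanently, against section 7.5's own preference for continuing.

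One practical objection stands in part: the protocol does not define who could become pregnant. If a definition is unwelcome, testing every female in the two drug arms avoids it, and the ceiling of 360 strips still holds.

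**Conclusion.** The point holds in limited form. No scheduled test can trigger the pregnancy stop in time to prevent re-dispensing at V2, V3 or V4, so a drug-arm woman with an unrecognised, unintended pregnancy could be given more drug at any of those visits. The reading of the schedule is firm. The number of women concerned is unknown, and no count of pregnancies or harms is offered. The conclusion rests on the protocol's own rule that pregnancy always ends treatment, not on any outside risk figure. It is a minor safety improvement, worth making because it costs so little, and it has no bearing on the trial's outcomes or analysis.

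**What to change.** 1. In section 1.2, mark the pregnancy-test row at V2, V3 and V4. Add a note limiting these three tests to females who could become pregnant in the pioglitazone and berberine groups.
2. In the laboratory lists of sections 9.3, 9.4 and 9.5, add a urine pregnancy test for the same women, done on the urine already collected for urine routine and read before drug is dispensed.
3. Leave section 7.5.2 as it is. A positive urine test then leads to drug being withheld pending the serum test named there.
4. Leave the V1 and V5 tests as they are in all arms.

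The text cost is three marks, one note and one added item in each of three visit lists. The running cost is three strips per woman concerned, at most 360 for the trial, and a short wait before dispensing. The no-drug arm has no extra tests, and no extra visit or invasive procedure is needed.
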